# Effect of a home‐based physical activity program on metabolic syndrome in Ghanaian adults with type 2 diabetes: Protocol for a feasibility randomized controlled trial

**DOI:** 10.1002/nop2.2180

**Published:** 2024-05-23

**Keywords:** exercise, metabolic syndrome, physical activity, randomized controlled trial, type 2 diabetes

## Abstract

**Aim:**

To describe the protocol of a feasibility trial designed to test the preliminary effect of a 12‐week culturally appropriate physical activity programme on metabolic syndrome markers and quality of life in Ghanaian adults with type 2 diabetes (T2DM).

**Design:**

Feasibility randomised controlled trial.

**Methods:**

Through random allocation, 90 adults with T2DM will be allocated to either the control group (CG) (*n* = 45) or the intervention group (IG) (*n* = 45). The IG will receive the physical activity programme in addition to their usual diabetes care; those in the CG will receive their usual diabetes care. Measurements will be performed at baseline and 12‐week follow‐up. The primary outcome is a change in metabolic syndrome markers in the IG compared to the CG. Secondary outcomes are: (a) a change in quality of life in the IG compared to the CG, (b) the feasibility of implementation.

**Results:**

Findings will inform the design of a future large‐scale trial.

**Patient or Public Contribution:**

Patients with T2DM and their healthcare professionals contributed to this study protocol by participating in semi‐structured interviews towards the design of the physical activity programme.

**Clinical Trial Registration Number:**

The trial is registered in the Australian and New Zealand Clinical Trial Registry (registration number: ACTRN12622000323729p).

## INTRODUCTION

1

Type 2 diabetes mellitus (T2DM) is a metabolic disorder characterised by the inability of the body to use insulin properly (Aschner, 2017). About 79% of adults with diabetes live in low‐resource countries, and the number of adults with T2DM is projected to increase faster in those countries (69% increase) compared to developed countries (20% increase) (International Diabetes Federation, 2019; NCD‐Risk‐Factor‐Collaboration, 2016). Similarly, 80% of deaths associated with diabetes occur in low‐ and middle‐income countries (International Diabetes Federation, 2019).

Over the past few decades, there has been a significant rise in both T2DM prevalence and T2DM‐related deaths in Ghana (Sarfo‐Kantanka et al., 2019). T2DM is one of the leading causes of morbidity and mortality in Ghana (Ghana Health Service, 2018), and a significant number of T2DM cases are often diagnosed at a later stage when disease complications are evident (Danquah et al., 2018). A study by Agyemang‐Yeboah et al. (2019), conducted at the Komfo Anokye Teaching Hospital in Ghana, found approximately 90% of individuals with T2DM in that hospital had metabolic syndrome (MetS); a constellation of cardiovascular risk factors that increases an individual's risk for cardiovascular disease (CVD), stroke and kidney failure (Chuang et al., 2019).

The use of medication alone in the management of T2DM has rarely been successful; hence, healthy lifestyle behaviours are encouraged (Davies et al., 2018). Despite the health benefits of physical activity (PA), most people with T2DM, especially those in low‐ and middle‐income countries, do not meet the recommended daily exercise of at least 120 min of moderate intensity or 75 min of vigorous intensity per week of PA (Oyewole et al., 2014). PA participation is enhanced when programmes are designed with consideration of socio‐cultural norms (Chaabane et al., 2021).

There is lack of evidence on effective PA programmes for people with T2DM in the African context, especially Ghana. Currently, there is no exercise programme in Ghana available for people with T2DM. This underscores the need for the development and testing of a PA programme to improve MetS markers in people with T2DM. The culturally appropriate home‐based PA programme to be evaluated in the current study is informed by the findings of two of our previous studies (Amin et al., 2023a, 2023b). Testing such programme before full implementation in a larger population provides evidence about its efficacy, possible participation rate and safety.

This paper describes the protocol for a feasibility randomised controlled trial (RCT) designed to test the preliminary effect of a 12‐week culturally appropriate home‐based PA programme on metabolic syndrome (MetS) markers and quality of life (QoL) in Ghanaian adults with T2DM. A secondary objective is to evaluate the feasibility of the PA programme. Thus, the findings from this study will provide preliminary evidence to inform the design of a larger multicentre RCT leading to the adoption of a feasible and effective PA programme for Ghanaian adults with T2DM.

## METHODS

2

### Trial design

2.1

This study is a single‐site parallel feasibility RCT in which participants will be randomly assigned to either an intervention group (IG) or control group (CG).

### Setting

2.2

The study will be conducted at the National Diabetes Management and Research Centre (NDMRC), Korle‐Bu Teaching Hospital in Ghana, a country with a national diabetes prevalence rate of 5.0% (International Diabetes Federation, 2019). The number of patients who visit the NDMRC annually is approximately 23,269 (Korle‐Bu‐Teaching‐Hospital, 2016). The outpatient clinic is open Monday to Friday excluding national holidays, with approximately 70 patients per clinic day (personal communication, [name], September 2020).

### Study population

2.3

The sample will include 90 Ghanaian sedentary adults with T2DM and MetS seeking care at the NDMRC. As the sample will be Ghanaian adults with T2DM and MetS, purposive sampling will be used for participant recruitment. For this study, T2DM diagnosis will be confirmed by the participant's physician or nurse at the NDMRC. MetS will be determined according to the definition of the National Cholesterol Education Programme (NCEP) Adult Treatment Panel (ATP) III (Adult‐Treatment‐Panel‐III, 2002). This definition has previously been used in a study conducted in Ghana (Agyemang‐Yeboah et al., 2019).

### Eligibility criteria

2.4

For participants to be included in the study, they must: (a) have a diagnosis of T2DM; (b) have MetS; (c) receive medical clearance provided by their physician to participate in the exercise programme; (d) have resided in Ghana for at least 2 years; (e) be at least 18 years of age and (f) be sedentary (not achieving 600 metabolic equivalent of task – minutes/week), based on the International Physical Activity Questionnaire – short form (IPAQ‐SF) assessment (Craig et al., 2003).

The following are the exclusion criteria: (a) current medical conditions that preclude physical activity (e.g., significant cardiac/respiratory diseases, severe osteoarthritis or arthritis, angina episodes during rest or with minimal exertion, significant vision loss and limb amputation); (b) frailty index score >3; (c) inability to travel to the NDMRC for supervised training; (d) no access to a mobile phone; or (e) pregnancy.

### Study enrolment, recruitment, and screening procedure

2.5

An enrolment target of 90 individuals with T2DM will be sought over a 3‐month period, with a target of 30 participants per month. Two recruitment approaches will be used: (a) nurses and consulting physicians at the NDMRC will identify potential participants who visit the NDMRC for their routine diabetes management, and (b) a study flyer will be displayed at the NDMRC.

At the pre‐screening stage, if a potential participant sees the flyer and is interested in the study, they will contact the researcher via the contact details on the flyer, or if they are at the NDMRC, they will speak to a nurse or physician about their interest in taking part in the study. The potential participant will be referred to a research assistant who is independent of the client's care team. If the research assistant identifies the person to be suitable for the study, they will introduce the study to that potential participant and provide them with a Participant Information and Consent Form (PICF). For participants who cannot read, the research assistant will read the PICF in the local language. The research assistant will answer any question that participants may have about the study.

Participants will be encouraged to discuss their involvement in the study with friends, family and other doctors. The research assistant will emphasise the voluntary nature of the study and how their inability to participate will in no way affect the services they receive at the NDMRC. They will also emphasise that participants have the right to discontinue participation in the study at any time before the data has been analysed.

Physicians at the NDMRC will determine whether individuals are able to participate in an exercise programme, as designed for this study. They will review the patient's medical record and provide a medical clearance note on their medical record.

#### Screening visit

2.5.1

Individuals who are identified as eligible to participate in the study and who express interest in taking part in the study will be invited to a screening visit. At the visit, the research assistant will complete the eligibility screening checklist. If a participant does not meet all the eligibility criteria, they will be ineligible to enrol in the study. Participants who meet the eligibility criteria will be invited to a baseline visit, where additional baseline testing and randomisation will be done.

### Informed consent

2.6

Prior to laboratory testing, history taking and physical examination, eligible participants will be required to provide their written consent. The research assistant will obtain written consent during the screening visit at the NDMRC. Participants will provide their consent to participate in the study by signing a written consent form.

### Randomisation

2.7

Through random allocation, 90 participants will be allocated to the CG (*n* = 45) or IG (*n* = 45). A computer‐generated randomisation sequence using EXCEL will be performed with a 1:1 allocation: an equal number of participants in the IG and CG groups. This randomisation will be done by the lead researcher, who has no contact with the hospital or participants. The randomisation sequence will be uploaded into REDCap. After the participant provides their consent, a nurse who is independent of the recruitment process will access the randomisation group from REDCap and advise the participant of their allocated group, either CG or IG.

Due to the nature of the intervention, participant blinding cannot be achieved. However, outcome assessors will be blinded to the group. Different assessors will perform the baseline and 12‐week follow‐up assessments to further reduce the risk of bias.

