#### Primary measures

2.9.1

The primary outcome is a change in MetS markers (BP, TG, WC, FBG and HDL) in Ghanaian adults with T2DM who participate in a 12‐week PA programme, compared to those who receive usual diabetes care.

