#### 6‐Minute walk test

2.10.7

The PT will take participants through a *6‐Minute Walk Test* (6MWT) to test their exercise capacity at baseline and 12‐week follow‐up. It assesses baseline functional capacity and cardiovascular risk, which are necessary in prescribing exercise intensity for patients (Amaricai, 2020). The walk test supports the prescription of an effective and safe exercise programme for people with T2DM (Nolen‐Doerr et al., 2018). A study among patients with T2DM showed a high interclass correlation coefficient for the 6MWT (Alfonso‐Rosa et al., 2014).

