### Data collection procedure

2.11

Data relating to demographics, eligibility screening, PA levels and QoL will be collected using online questionnaires. A nurse or research team member who is independent of the participant's care team will provide the participant with a quiet place at the NDMRC and administer the eligibility screening checklist. Similarly, the nurse will follow the same procedure to administer the baseline demographic data questionnaire and the baseline and week‐12 follow‐up IPAQ—SF and SF‐12V2 questionnaires. If a participant is unable to read and/or write in English, the nurse will administer the questionnaires verbally in the local language. Surveys will be completed electronically via a RedCap survey tool.

Prior to each exercise session at the physiotherapy centre, the PT will measure the IG participants' BP, HR and random blood glucose (RBG) using the hospital's standard procedure.

WC will be taken by measuring the mid‐point between the lower costal margin and iliac crest.

A 5‐mL sample of venous blood will be collected after at least an 8‐h overnight fast. Participants will be advised about the need for the overnight fast in the PICF and will be sent a reminder via text. A senior biomedical scientist will collect blood samples and biochemical tests (TG, HDL and FBG) will be performed using the hospital's standard protocol. Blood sample will be collected into a serum separation tube and analysed using a dry chemistry analyser.

During the participants' weekly visit to the physiotherapy department, the PT will assess exercise participation and safety using a checklist for exercise participation and the participants' exercise diary. Measures of participation will be determined by the percentage of sessions attended and the proportion of participants who complete the prescribed PA: 22 sessions of home‐based aerobic exercises and 14 sessions of facility‐based resistance training. An overall score <50% of attendance will be judged as low participation and above 70% will be graded as high participation. A score between 50% and 70% will be graded as moderate participation. Reasons for non‐participation or withdrawal will be documented.

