### Data analysis

2.13

Data analysis will be performed using the latest version of STATA. Feasibility outcomes will be summarised using descriptive statistics such as frequencies, percentages, mean, SD, median and interquartile range. Relevant parametric and non‐parametric repeated measure analyses will be undertaken to measure between groups differences and changes in effect between and within the two groups. Specifically, the student's *t*‐test will be used for comparing the IG and CG. Between group analysis will be conducted using Pearson's chi‐square and Mann‐Whitney tests for categorical and continuous variables, respectively. A *p*‐value of <0.05 will be considered statistically significant. To obtain the overall effect of the PA intervention on MetS markers, the MetS score for each participant will be assessed. The MetS score is a useful measure of MetS severity, and it correlates to the severity of CVD (Solymoss et al., 2004). The MetS Z‐score will be calculated by adding the MetS risk components for each participant. The MetS Z‐score would be used to measure the change in MetS severity (DeBoer et al., 2018). Further, the effect of the programme on individual MetS markers will also be examined.

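### With assessors switched between baseline and week 12, within-group changes in operator-dependent markers cannot be told apart from assessor differences; the randomised comparison is not affected if assessors are balanced over arms

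*Protocol article*

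**What the plan says.** - **Assessors (section 2.7, Randomisation).** The article says that "outcome assessors will be blinded to the group" and adds a second safeguard: "Different assessors will perform the baseline and 12‐week follow‐up assessments to further reduce the risk of bias".
- **Outcome (section 2.9.1, Primary measures).** "The primary outcome is a change in MetS markers (BP, TG, WC, FBG and HDL"), in the programme arm compared with usual care.
- **How the markers are measured (section 2.11, Data collection procedure).** Waist circumference is taken by hand at an anatomical site: "WC will be taken by measuring the mid‐point between the lower costal margin and iliac crest". Triglycerides, HDL and fasting glucose come from venous blood "analysed using a dry chemistry analyser". The article does not say whether blood pressure is read manually or by an automatic device.
- **Analysis (section 2.13, Data analysis).** The plan is to "measure between groups differences and changes in effect between and within the two groups", with a significance threshold of 0.05. A composite is also planned: "The MetS Z‐score will be calculated by adding the MetS risk components for each participant".
- **Other assessments.** Section 2.10.7 has the physical therapist run the walk test "to test their exercise capacity at baseline and 12‐week follow‐up", and section 2.11 has the nurse administer both rounds of questionnaires. These are roles, so different individuals could fill them at the two visits. The article does not say how the different-assessor rule applies to them.

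**The concern.** For a measurement that depends on who takes it, the observed change has two parts: what happened to the participant, and the difference between the two people who measured. If the person changes between visits for everyone, those parts are fully aligned with each other. A before-after test within one arm then responds to either, and no later analysis can separate them unless there are duplicate readings or some other link between assessors.

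This matters because section 2.13 includes within-group change in the analysis, and the Discussion says the results will show whether there is a trend towards improvement. A fall in waist circumference in the intervention arm that came only from the switch of assessor could be reported as a significant improvement. The trial is also meant to supply a variance for the larger trial, so it matters whether the rule adds noise.

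**Working it through.** **1. The plan's own figure.** Section 2.12 aims for 72 participants and allows 20% for attrition: 72 / (1 − 0.20) = 90, or 45 per arm. This reproduces the stated target. The corresponding number of completers is 36 per arm, which is used below.

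**2. Model.** Observed change = true change + (week-12 assessor effect − baseline assessor effect) + residual. With one assessor per visit, the middle term is a constant shift *b*, so:

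- the within-arm mean change estimates true change + *b*;
- the between-arm difference estimates (true change in intervention + *b*) − (true change in control + *b*), and *b* cancels.

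**3. Size of the within-group effect.** The documents give neither an assessor difference nor an SD of change, so *b* is an assumption, expressed in SDs of change from 0 to 0.5. The within-group test is taken as a two-sided one-sample t-test at 0.05 with n = 36 and no true change. The article names no such test and does not state sidedness, so both are assumptions too. The noncentrality is *b* × √36 = 6*b*, with 35 degrees of freedom. The between-group rate comes from 20,000 simulated trials with a two-sample t-test and the same *b* in both arms.

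| Shift *b* (SD of change) | Noncentrality | Within-group false-positive rate, exact | Same, simulated | Between-group rate, simulated |
|---|---|---|---|---|
| 0 | 0 | 5.0% | 5.0% | 5.0% |
| 0.1 | 0.6 | 9.0% | 9.2% | 5.3% |
| 0.2 | 1.2 | 21.5% | 21.9% | 5.2% |
| 0.3 | 1.8 | 41.7% | 41.6% | 4.7% |
| 0.5 | 3.0 | 83.1% | 83.4% | 4.8% |

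In centimetres, again by assumption: if the SD of change in waist circumference were 5 cm, a 1 cm assessor difference would be 0.2 SD.

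**4. Variance.** With a single assessor at each visit, *b* is constant and adds nothing to the variance of change. If several assessors rotate at each visit, each change carries two independent assessor effects. Its variance then becomes 1 + 2*r* times the original, where *r* is assessor variance divided by the variance of change without assessor error. Take a difference of 2.8016 × √(2/36) = 0.66 SD, which has 80% power at 36 per arm without assessor error. For assumed *r*:

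| *r* | SD of change multiplied by √(1 + 2*r*) | Power at 36 per arm | n per arm for 80%, 36 × (1 + 2*r*) rounded up |
|---|---|---|---|
| 0.05 | 1.049 | 76% | 40 |
| 0.1 | 1.095 | 73% | 44 |
| 0.2 | 1.183 | 66% | 51 |
| 0.3 | 1.265 | 60% | 58 |

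The article does not give the number of assessors, so this second table applies only if they rotate.

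**5. Which markers are exposed.** Waist circumference is, by its description. Blood pressure is if it is taken manually. The Z-score is through those components. Triglycerides, HDL and fasting glucose are analyser results and depend little on who conducts the visit.

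**The case against.** The strongest defence is that the rule protects what matters most. Section 2.5.1 places randomisation at the baseline visit, and section 2.8.1 places the education session there as well. Someone who measures at that visit may learn the allocation or remember the baseline reading. A fresh assessor at week 12 guards against both, and so protects the randomised comparison at the price of some within-group comparability. That stands: the rule is a defensible trade-off, and a mandatory same-assessor rule would give something up.

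It is also fair to say that the outcomes are defined as intervention compared with control, that the t-test is assigned to that comparison, and that no paired test is named. This limits the weight of the point. It does not remove it, because section 2.13 expressly includes change within the groups.

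A third argument is that using the same assessor would not make within-group change causal. Time, usual care and regression to the mean in people selected for having metabolic syndrome would remain. That is correct, and it supports descriptive reporting whoever measures.

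Finally, assessor training and standardisation may be set out in the full protocol, which is not shown. Their absence from the article is no evidence that the shift is large.

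**Conclusion.** The point holds in a limited form, at low severity. Under the rule in section 2.7, within-group changes in waist circumference, in blood pressure if taken manually, and in the Z-score built on them cannot be separated from a systematic assessor difference. Significance tests on them are therefore not interpretable. For shifts of 0.1 to 0.5 SD of change and 36 completers, the false-positive rate would be about 9% to 83% instead of 5%. The sizes of the shift are assumptions, and the form of the within-group test is inferred from a loosely worded sentence.

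A reader might infer more, and the documents do not support it:

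- **That every change score is affected.** Three of the five primary markers are laboratory results.
- **That the primary comparison is biased.** A shift common to both arms cancels. Bias would need assessors to be distributed differently by arm, and nothing in the text suggests this.
- **That the variance passed to the larger trial is inflated.** This follows only if several assessors rotate, which the article does not say.
- **That the different-assessor rule is itself a mistake.** It has a sound purpose in protecting blinding at follow-up.

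**What to change.** Two short changes:

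1. **Section 2.13:** state that within-group changes are reported descriptively, without significance claims, and that all conclusions rest on the intervention-versus-control comparison.
2. **Section 2.7:** state that, at each time point, the same blinded assessor or assessors measure both arms. This secures the cancellation on which the between-group comparison relies.

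Using the same assessor for both visits of a participant is an option where that person can be kept away from allocation and is available at week 12. It should not be a requirement.

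The cost is a sentence in each section, minor rota planning, and the loss of within-group significance claims. The randomised comparison loses nothing.
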